### Data monitoring

A data monitoring committee was not included because the trial involves a behavioural intervention (progressive exercise) with known/minimal risks, and does not require periodic benefit–risk assessments. No independent auditing of trial conduct is planned.

### Confidentiality

In order to maintain confidentiality during and after the trial, all study-related information will be stored securely at the study site in areas with limited access. Furthermore, access within the study team will be the minimum required for data analysis and quality control. Blood samples, electronic files, data sheets and completed questionnaires will be stored using coded IDs. Digital files will be stored on password-protected computers, in password protected folders, and backed up on a password-protected hard drive. Records that contain personal identifiers (such as informed consent forms) will be stored separately from those identified by coded ID, in a locked cabinet in an office accessible to the study co-ordinator.

### Data analysis

#### Neuromuscular data

The potentiated mechanical response from a single electrical stimulus will be analysed for amplitude of the twitch (Q_tw,pot_), maximal rate of force development and maximal relaxation rate. Voluntary activation using femoral nerve electrical stimulation (VA_FNES_) will be calculated using the interpolated twitch technique where the amplitude of the SIT is normalized to the corresponding Q_tw,pot_ using the equation VA_FNES_ (%) = (1-(SIT/Q_tw.pot_)) × 100 [60]. For TMS, an estimated resting twitch (ERT) will be calculated by taking the y-intercept of a linear regression of the SIT-voluntary force relationship. VA_TMS_ will be subsequently quantified using the equation VA_TMS_ (%) = (1-(SIT/ERT)) × 100 [118]. Where regressions are not linear (defined as *r* < 0.9 [119]), those data will be excluded.

For the evoked EMG responses, the peak-to-peak amplitude and area under the curve of the MEP in all muscle groups will be determined from a selection of data encompassing the biphasic wave. The selection will begin at the first deviation from zero after any stimulation artefact, and end on the return to zero after the biphasic wave. The M-waves evoked in the VL and RF will be analysed using the same method. For the assessment of corticospinal excitability, the VL and RF MEPs will be normalised to an M-wave delivered during a contraction and nearby in time_._ The silent period will be measured from stimulus artefact to the continuous resumption of voluntary EMG, determined by an experimenter experienced in the analysis, using visual inspection of the EMG trace [120].

#### Heart rate variability

In the time domain (ms), the mean normal-to-normal (NN) interval, the standard deviation of the average NN interval (SDNN) and the square root of the mean squared differences of successive NN intervals (RMSSD) will be calculated. As recommended for short-term HRV recordings [115], the spectral components analyzed in the frequency domain (ms^2^) will be the very low frequency (VLF; 0.01–0.04 Hz), low-frequency (LF; 0.04–0.15 Hz) and high-frequency (HF; 0.15–0.40 Hz). The LF/HF ratio will also be calculated. The spectral analysis will be performed using fast Fourier transform algorithms (Kubios HRV Standard v3.0.2).

#### Actigraphy

The night following Visit #1 will be excluded from the actigraphy data analysis to mitigate any effect of acute maximal exercise (which participants are likely to be unaccustomed to). Data will be analysed using MotionWare 1.0.27 (CamNtech, UK). Responses from the sleep log will be used to confirm the start and end time of the sleep window, activity onset/offset and “lights out”/“lights on” (as determined by the light sensor). Sleep parameters calculated within the software include time in bed, actual sleep time, actual wake time, sleep efficiency (the percentage of time in bed spent sleeping), sleep-onset latency (time from “lights out” to sleep onset), fragmentation index (the percentage of immobile phases of one minute). For rest-activity cycle characteristics, the following parameters will be calculated using a non-parametric circadian rhythm analysis option [121]: relative amplitude (calculated from estimated lowest and highest activity periods), inter-daily stability (the degree of regularity of the rest-activity patterns on individual days in the 24 h environment), intra-daily variability (the fragmentation of periods of rest and activity), the estimated peak time of activity period, mesor (mean level), L5 (mean activity counts in the least active 5 h period in the average 24 h pattern) and L5 mid (the central time of the L5 period, usually referring to the trough of the rest-activity cycle). The mean amount of activity during the sleep period and the activity index (percentage of 30-s epoch during both sleep and wake periods with an activity > 0) will be calculated from extracted raw data. An objective measure of day-time physical activity will be computed as the number of minutes spent at sedentary, light and moderate-to-vigorous physical activity intensities over the 14-day measurement period. This will be quantified using calibrated cut-points for MotionWatch 8© activity counts, as determined in healthy older adults [122].

### Intended statistical analysis

Data will be analysed after data collection is complete, and no interim statistical analysis will be performed. Descriptive statistics will be used for demographic and clinical variables measured at baseline for each group. Frequencies and percentages will be used for categorical variables and the mean ± standard deviation (or median and range) will be used for continuous variables. To account for any differences in loss to follow up between groups, the primary analysis will be conducted on an intention-to-treat basis. For the primary outcome of FACIT-F score between treatment arms over time, data will be analysed with linear mixed models using R [123] and lme4 [124]. “Treatment arm” will be included as a fixed effect and “participant” as a random effect. Parameters will be estimated using restricted maximal likelihood. The Kenward-Roger approximation for degrees of freedom will be used when evaluating the significance of effects. This produces optimal type I error rates (neither anti-conservative nor overly sensitive to sample size) [125]. Secondary analyses will be performed to assess adjustments for protocol deviations (per protocol analysis). Statistical code will be made openly available upon publication of the results. A minimum of a 3-point difference in FACIT-F score will be considered clinically relevant [126]. For secondary outcomes that are assessed pre- and post-intervention only (e.g. neuromuscular measures, sleep parameters, blood biomarkers), two-way mixed design ANOVA will be used (group [tailored vs. traditional] × time [pre- vs. post-intervention]). In this case, missing data will be dealt with using list-wise deletion. Following a significant interaction, pairwise comparisons will be conducted with a Bonferroni adjustment. The threshold for rejecting the null hypothesis will be *p* < 0.05. For main and interaction effects, partial eta squared will be computed as an effect size estimate. Effect sizes for pairwise comparisons will be reported as Cohen’s *d* [127, 128]. This will be supplemented with 95% confidence intervals for mean differences. Further exploratory analysis will be labelled as such in later reporting.

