In summary, while generic exercise recommendations are likely sufficient for the majority of cancer survivors after treatment, tailoring of interventions may be warranted in cancer survivors with persistent CRF. Indeed, it has previously been suggested that interventions should be tailored according to the specific health outcome [62]. Here, we propose a comprehensive pre-intervention assessment including a number of pathways by which exercise may alleviate CRF, via improvements in physiological parameters or sleep. Based on objective assessments including cardiorespiratory fitness, neuromuscular function and sleep (actigraphy), a tailored exercise intervention will be designed based on individual deficits or areas for improvement. The primary aim of this research is to investigate the effect of a traditional vs. tailored 12-week exercise intervention on self-reported CRF severity (FACIT-F score) in cancer survivors with persistent CRF. We hypothesize that there will be an improvement in CRF after the exercise intervention in both groups, and that the improvement will be greater in the tailored vs. traditional exercise intervention.

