### Sample size

An a priori sample size estimation was performed using G*Power 3 (v3.1.2–3.1.9 [66]). The hypothesis was treated as a time × treatment (within-between) interaction for the primary outcome measure of score on the FACIT-F. A standardized mean difference of 0.44 was used, as reported in a 2012 Cochrane review for comparisons of CRF following an exercise intervention or control, from a total of 539 cancer survivors after anti-cancer therapy [29]. Using an α level of 0.05, a 1 - β of 0.8, the total sample size was calculated as 44. Potential loss to attrition was estimated as 15%, based on previous reports from supervised exercise interventions in cancer survivors post-treatment (e.g. [67]), and thus the total sample size was calculated as 52.

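### The terms listed for the primary FACIT-F mixed model include no time, arm-by-time or baseline term, so as written they do not test the interaction on which the trial is sized

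*Protocol article*

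**What the plan says.** The hypothesis concerns change. The Background section of the protocol article expects both arms to improve and states that "the improvement will be greater in the tailored vs. traditional exercise intervention". The Sample size section turns this into a test: "The hypothesis was treated as a time × treatment (within-between) interaction for the primary outcome measure of score on the FACIT-F". It takes the effect size from a published meta-analysis ("A standardized mean difference of 0.44 was used") and continues: "Using an α level of 0.05, a 1 - β of 0.8, the total sample size was calculated as 44". Allowing for 15% attrition raises the total to 52.

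The Intended statistical analysis section introduces the primary analysis as follows: "For the primary outcome of FACIT-F score between treatment arms over time, data will be analysed with linear mixed models". The next sentence gives the terms: "Treatment arm” will be included as a fixed effect and “participant” as a random effect". Estimation is by REML with Kenward-Roger degrees of freedom. No time effect, arm-by-time interaction or baseline covariate is listed. For the secondary outcomes measured only before and after the intervention, the same section does write out a group-by-time design.

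Table 2 schedules FACIT-F at recruitment, Lab Visit #2, weeks 3, 6 and 9, Lab Visit #4, and months 6 and 12. The Randomization section places allocation after Lab Visit #2. The article does not say which of these scores are outcome rows in the primary model.

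**The concern.** A difference in improvement is carried by an arm-by-time term, or by a comparison of later scores adjusted for baseline. A model with arm as the listed fixed effect and a participant random intercept contains neither. Its arm coefficient compares the average level of FACIT-F between arms over whatever scores are entered.

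If the Lab Visit #2 score is one of those, the average includes an occasion before randomization at which the expected difference is zero. The estimate is then pulled toward zero, and any chance imbalance at baseline enters it directly. The test that decides the trial would not be the one for which the 44 participants were calculated.

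**Working it through.** **Inputs.** From the Sample size section: SMD 0.44, α 0.05, power 0.80, total 44, attrition 15%. From Methods/design: 1:1 allocation. From Table 2: the FACIT-F schedule. Assumed, because the article does not give them: the conversion f = SMD/2, two measurements in the sample-size calculation, a common within-person correlation ρ (0.5, range 0.3 to 0.7), and the shape of the effect over time.

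**1. Reproduce the plan's 44.** For a within-between interaction with two groups and m measurements, λ = f²·N·m/(1−ρ), with 1 and N−2 degrees of freedom when m = 2. With f = 0.44/2 = 0.22, m = 2 and ρ = 0.5, N = 44 gives λ = 0.0484 × 44 × 2/0.5 = 8.52 and power 0.814. N = 42 gives 0.795, so 44 is the smallest even total. Then 44/0.85 = 51.8, rounded up to 52. Alternatives do not give 44: five measurements need 26 in total, and a plain two-sample comparison at SMD 0.44 needs 82 per arm. The stated 44 therefore fits a pre/post arm-by-time test.

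**2. The difference to which this corresponds.** The equivalent t test on change has noncentrality δ/[√(2(1−ρ))·√(4/N)]. Its square, δ²N/[8(1−ρ)], equals λ when δ = 4f = 0.88 SD. This δ is used below so that the two models are compared at the effect for which 44 does give about 81% power at ρ = 0.5.

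**3. What the arm coefficient estimates.** With balanced data, the arm-only random-intercept estimate is the difference between arms in participant means, that is, δ times the mean of the effect profile:

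- Lab Visit #2 and Lab Visit #4: (0, 1), mean 0.50.
- Weeks 0 to 12 with linear build-up: (0, 0.25, 0.5, 0.75, 1), mean 2.5/5 = 0.50.
- The same plus months 6 and 12 with the effect fully maintained: mean 4.5/7 = 0.643.
- Without the baseline row, weeks 3 to 12: mean 2.5/4 = 0.625; with months 6 and 12 added: 4.5/6 = 0.75.

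**4. Power at N = 44, δ = 0.88 SD.** The participant mean has SD √(ρ + (1−ρ)/m), and the noncentrality is (profile mean × 0.88)/(SD × √(4/44)), with 42 degrees of freedom. Example, pre/post at ρ = 0.5: 0.44/(0.866 × 0.3015) = 1.685, power 0.377. The interaction at ρ = 0.5: 0.88/(1 × 0.3015) = 2.919, power 0.814.

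| Test and outcome rows | ρ = 0.3 | ρ = 0.5 | ρ = 0.7 |
|---|---|---|---|
| Arm-by-time interaction, pre/post | 0.67 | 0.81 | 0.96 |
| Arm only, pre/post | 0.42 | 0.38 | 0.34 |
| Arm only, weeks 0–12 | 0.58 | 0.45 | 0.37 |
| Arm only, through month 12 | 0.83 | 0.68 | 0.57 |
| Arm only, weeks 3–12, no baseline row | 0.73 | 0.62 | 0.53 |
| Arm only, week 3 to month 12, no baseline row | 0.91 | 0.80 | 0.69 |

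**5. Simulation check.** In 400 simulated pre/post trials (N = 44, ρ = 0.5, true difference 0.88 SD), the arm-only mixed model gave a mean coefficient of 0.46 SD and rejected in 39.5%. The model with arm, time and arm-by-time gave 0.88 SD and rejected in 82.5%. Both agree with the formulas.

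**The case against.** The strongest reply is that the sentence is an incomplete list and not a committed wrong model. The article never says that arm is the only fixed effect. The preceding sentence speaks of FACIT-F between arms over time, the Kenward-Roger sentence refers to effects in the plural, and the Sample size section names the interaction. A condensed article may leave the full formula to an analysis plan that is not shown. This has weight: a reader might infer that the trial has adopted an arm-only model, and the document does not support that. What stands is that the article did choose to list the terms, down to the estimation method and degrees of freedom, and left out the one that carries the hypothesis while writing out group × time for secondary outcomes.

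A second reply is that the dilution needs the Lab Visit #2 score as an outcome row, which is nowhere stated. That is correct. A reader might infer that the primary estimate is halved and power lost in every case, but the table shows otherwise. At ρ = 0.3 the arm-only test through month 12 has power 0.83 against 0.67 for the pre/post interaction. Without a baseline row, arm-only power at ρ = 0.5 is 0.62 to 0.80.

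A third reply concerns the deciding time point. A reader might count eight possible occasions, but the recruitment score is an eligibility screen and nothing suggests that it enters the model. The aim is framed around a 12-week intervention, and months 6 and 12 are set apart as follow-up. The end of the intervention is signposted, although no sentence names it as the primary contrast.

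**Conclusion.** The point holds as an inconsistency within the article: the terms listed for the primary model do not test the interaction on which the trial is sized, or the greater improvement that it hypothesizes. A drafting omission is a plausible explanation. The inconsistency itself needs no assumption about correlation or effect shape, and it remains whichever visits are entered.

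The numerical consequences are conditional on the listed terms being fitted literally. With Lab Visit #2 as an outcome row, the arm coefficient would be about 50% of the end-of-intervention difference (pre/post, or weeks 0–12 with linear build-up) or about 64% (through month 12, effect sustained). Pre/post power falls well short of the interaction's at every correlation examined. Across the other layouts the loss ranges from large to none. Even where power is not lost, the arm term estimates an average level difference and not a difference in improvement.

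**What to change.** In Intended statistical analysis, state the primary model with arm, visit and arm-by-visit as fixed effects and participant as a random effect. A model for post-baseline scores adjusted for the Lab Visit #2 score would serve equally well. Say that Lab Visit #2 is the baseline and that the recruitment screening score is excluded. Name one primary contrast, the tailored minus traditional difference in change from Lab Visit #2 to Lab Visit #4, in line with the 12-week aim, and make months 6 and 12 secondary.

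The cost is two or three sentences and a change to the R formula. No extra data or participants are needed. The change should be documented before the data are analysed.

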## Methods/design

This study is a prospective randomized controlled trial with a two-armed parallel design and 1:1 allocation ratio. Flow through the study is presented in Fig. 1. This study has been approved by the Health Research Ethics Board of Alberta Cancer Committee (HREBA.CC-16-10-10). The approved study will be reviewed annually by the HREBA.CC until completion. Any amendment to the protocol which may impact on the conduct of the study will require formal modification and approval by the HREBA.CC prior to implementation, and will be described transparently in subsequent reports. The study will be performed according to the Declaration of Helsinki. The study was registered at ClinicalTrials.gov before recruitment of the first participant (NCT03049384, first posted in February, 2017). The research will be conducted at a single site (Faculty of Kinesiology, University of Calgary, Alberta, Canada). This study protocol is written in accordance with the SPIRIT guidelines [63] (SPIRIT Checklist provided in Additional file 1).

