### Randomization

Due to a continuous enrolment strategy and relatively small sample size, participants will be allocated to groups using a dynamic allocation procedure (minimization, performed using an open-source, online minimization program (MinimPy Program 0.3) [68]. In this process, the first participant is allocated randomly to one of two treatment groups. Each newly enrolled participant is hypothetically allocated to each treatment group and an imbalance score is calculated given unweighted baseline categorical variables: sex (male, female), age group (18–39, 40–49, 50–59, 60–75) and cancer type (breast, prostate, lung, colorectal, other). The participant will be allocated to the preferred group (least imbalance) with a 1:1 allocation ratio, and a randomisation weighting of 0.75 in order to avoid the potential introduction of bias associated with pure minimization [69]. Participants will be randomized following completion of all baseline assessments (i.e. after Lab Visit #2, see below), by a researcher who is independent of the recruitment, enrolment and laboratory assessment process, and who has password-protected access to the allocation procedure for the trial within the online minimization program.

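### The primary FACIT-F model names treatment arm as its only fixed effect and leaves out baseline FACIT-F and the minimisation factors, giving up precision that would cost almost nothing to keep

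*Protocol article*

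**What the plan says.** The *Randomization* section allocates participants by minimisation, with a 0.75 weighting towards the preferred arm, on "unweighted baseline categorical variables: sex (male, female), age group (18–39, 40–49, 50–59, 60–75) and cancer type (breast, prostate, lung, colorectal, other". Randomisation follows all baseline assessments. These include the FACIT-F completed at Lab Visit #2 (Table 2 and the *Cancer-related fatigue* subsection).

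For the primary outcome, *Intended statistical analysis* sets out a linear mixed model for FACIT-F between arms over time, fitted by restricted maximum likelihood with Kenward–Roger degrees of freedom. On its terms it says only that "Treatment arm” will be included as a fixed effect" and that participant is a random effect. It names no minimisation factor, no baseline covariate, and no time or arm × time term.

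The *Sample size* section points to a specific contrast: "The hypothesis was treated as a time × treatment (within-between) interaction for the primary outcome measure". It then states: "Using an α level of 0.05, a 1 - β of 0.8, the total sample size was calculated as 44".

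**The concern.** Two sources of precision are paid for in the design and not named in the analysis.

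- **Baseline FACIT-F.** This is the same scale as the outcome, taken before allocation, and is likely to be a strong predictor of the later score. Using it only as the first of several responses is less efficient than conditioning on it.
- **The minimisation factors.** Minimisation makes the arms more alike on these factors than simple randomisation would. If the factors predict the outcome, a between-participant comparison that omits them attaches a standard error that ignores the balance. That standard error is too large and the test is conservative. The Kenward–Roger method, which the section credits with good type I error control, corrects degrees of freedom and does not address this.

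What is at stake is power and interval width in a small trial. The risk is not one of false positives.

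**Working it through.** **1. The plan's own figure.** Inputs from *Sample size*: "A standardized mean difference of 0.44 was used", α 0.05, power 0.80, two arms 1:1. The number of measurements m = 2 and the correlation ρ = 0.5 are not stated and are assumed here. With f = 0.44/2 = 0.22, the noncentrality is f²·N·m/(1 − ρ) = 0.0484 × 44 × 2/0.5 = 8.52 on 1 and 42 degrees of freedom. Power is 0.814; at N = 42 it is 0.795. So 44 is reproduced, and 44/0.85 = 51.8 rounds up to 52. The figure therefore matches a pre/post interaction, which is the contrast used in step 2.

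**2. Baseline as a response or as a covariate.** Take a common SD σ, n per arm and pre–post correlation ρ (not given in the document).

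- Arm × time with baseline as an unconstrained response (equivalent to change from baseline): variance = 2σ²(1 − ρ) × 2/n.
- Baseline as a covariate: variance = σ²(1 − ρ²) × 2/n.
- Ratio of standard errors = √[2(1 − ρ)/(1 − ρ²)] = √[2/(1 + ρ)].

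| ρ (assumed) | SE ratio | 44 with the covariate is worth, by change score, 44 × 2/(1 + ρ) |
|---|---|---|
| 0.3 | 1.24 | 68 |
| 0.5 | 1.15 | 59 |
| 0.6 | 1.12 | 55 |
| 0.7 | 1.08 | 52 |
| 0.8 | 1.05 | 49 |

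**3. Minimisation factors: which effect is tested matters.** Simulation: 3,000 trials per setting, N = 44, the stated three-factor minimisation with weighting 0.75, no treatment effect, outcome SD 1 and ρ = 0.5. The category frequencies, and the share R² of outcome variance explained by the factors, are assumed. Adjustment uses every category: 1 + 3 + 4 = 8 degrees of freedom.

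*(a) Overall arm effect (mean of pre and post), the literal reading of arm as sole fixed effect:*

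| R² | Mean SE, unadjusted | True sampling SD, unadjusted | Mean SE, adjusted | Type I error, unadjusted | Type I error, adjusted |
|---|---|---|---|---|---|
| 0 | 0.260 | 0.260 | 0.273 | 0.052 | 0.047 |
| 0.1 | 0.260 | 0.253 | 0.253 | 0.043 | 0.052 |
| 0.2 | 0.261 | 0.231 | 0.234 | 0.029 | 0.048 |
| 0.3 | 0.261 | 0.227 | 0.210 | 0.027 | 0.048 |

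The unadjusted SE exceeds the adjusted one by 3%, 12% and 24% at R² 0.1, 0.2 and 0.3 (0.260/0.253, 0.261/0.234, 0.261/0.210). The simulation error of a 5% rate is √(0.05 × 0.95/3000) = 0.004, so the shortfall at R² 0.1 is not clearly distinguishable from chance; those at 0.2 and 0.3 are. For a comparison of post scores alone, unadjusted type I error is 0.046, 0.035 and 0.028.

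*(b) Arm × time:* a factor that is constant within a participant cancels from the change score. The SE is 0.300–0.301 whatever the R², and adding the factors as main effects does not alter it. Unadjusted type I error is 0.046–0.054. Random-intercept REML fits agree: 0.301 with and without a prognostic covariate.

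**4. Factors once baseline is a covariate.** With full 8-df coding the SE goes from 0.263 to 0.276 at R² 0, from 0.263 to 0.272 at 0.1, from 0.264 to 0.266 at 0.2 and from 0.263 to 0.256 at 0.3. The extra gain is small, and full coding can cost up to 5% (0.276/0.263). Compact coding (sex, age as one term, breast versus other) is cheaper: in a separate simulation of post scores without baseline, the SE rose only from 0.300 to 0.303 at R² 0.

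**The case against.** The best defence is that the trial's hypothesis is greater improvement in the tailored arm, which is an arm × time contrast. The *Sample size* section says so, and the analysis is described as running over time. In that model the participant random effect absorbs stable differences due to sex, age and cancer type. Step 3(b) confirms this. A reader might infer that the primary standard errors and confidence intervals are simply wrong. The documents do not support that for the interaction: the intervals are valid and type I error is near 5%.

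It is also fair to say that the sentence on fixed effects is condensed, since it omits time as well. A reader might infer that baseline FACIT-F is ignored altogether. That does not follow either, because baseline may well be one of the repeated responses. Finally, R² and ρ are not in the document, and with R² = 0 full adjustment makes the SE slightly worse.

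Two things remain. First, the section fixes the estimation method and degrees-of-freedom approximation, and spells out group × time for the secondary outcomes, yet names only arm for the primary one. The *Dissemination and data sharing policy* section describes the primary analysis as the effect of treatment arm. The literal between-participant reading is therefore open, and under it the conservatism is real. Second, the precision lost by using baseline as a response rather than a covariate applies under the charitable arm × time reading itself.

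**Conclusion.** The point holds as a loss of precision. Under an arm × time analysis with baseline as an unconstrained response, the SE is about 15% larger than it need be at ρ = 0.5, and 5–24% larger over ρ from 0.8 to 0.3. This assumes equal variances at the two visits and a single pre–post contrast. It is inefficiency, not an invalid interval.

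Under a between-participant arm test, omitting the minimisation factors additionally overstates the SE and pulls type I error to about 3–4% for R² of 0.1–0.3. That range is assumed, and the effect disappears if the factors are not prognostic. Any error is towards caution. The label is free improvement.

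**What to change.** Rewrite the primary model sentence before any outcome data are seen:

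- Model post-baseline FACIT-F with Lab Visit #2 FACIT-F as a continuous covariate, and with time, arm and arm × time as fixed effects. Alternatively, use a mixed model that keeps baseline as a response but constrains the arms to a common baseline mean. Say explicitly that baseline is not also kept as an unconstrained response.
- Name the contrast that is the primary treatment effect.
- Add sex, age (continuous) and cancer type as fixed effects. Fix the collapsing of cancer type in advance, for example breast / prostate / other, rather than letting observed cell counts decide it.

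Cost: one or two sentences and no new data. The terms use about 5 degrees of freedom (baseline 1, sex 1, age 1, three-level cancer type 2). If the factors turn out not to be prognostic, expect a very small rise in SE: about 1% with the compact coding in step 4, which has one cancer-type term fewer than proposed here, against about 5% with all 8 terms.

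### The terms listed for the primary mixed model omit time and arm × time, so the model as listed does not test the interaction on which the trial was sized

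*Protocol article*

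**What the plan says.** The Background section ends with the hypothesis that both arms will improve and "that the improvement will be greater in the tailored vs. traditional exercise intervention". That is a statement about a difference in change.

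The Sample size section follows it: "The hypothesis was treated as a time × treatment (within-between) interaction for the primary outcome measure of score on the FACIT-F". The total is 44 evaluable participants, raised to 52 for 15% attrition.

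The Intended statistical analysis section introduces the primary model with "For the primary outcome of FACIT-F score between treatment arms over time, data will be analysed with linear mixed models", and then gives its terms: "Treatment arm” will be included as a fixed effect and “participant” as a random effect". It goes on to REML and Kenward-Roger degrees of freedom, but names no time, arm × time or baseline-score term. For outcomes measured only before and after the intervention, the same section specifies a mixed-design ANOVA and does write out group × time.

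Table 2 places FACIT-F at recruitment, Lab Visit #2, weeks 3, 6 and 9, Lab Visit #4, and months 6 and 12. Under Randomization, allocation takes place after Lab Visit #2, so that score is a pre-randomisation baseline. On dropout, the analysis section states: "To account for any differences in loss to follow up between groups, the primary analysis will be conducted on an intention-to-treat basis". Under Treatment arms, no further outcome data are collected from participants who withdraw.

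**The concern.** In a random-intercept model whose only fixed term is arm, the arm coefficient is the difference between arms in participants' average score over whichever visits are rows. It is not a difference in improvement, and no other coefficient supplies one. The primary test would then answer a different question from the hypothesis and the sample size calculation.

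Two consequences follow. If Lab Visit #2 is one of the rows, a visit with no true arm difference is averaged into the estimate, which shrinks it. And because the model has no time term, an improvement common to both arms is not separated from who stays: an arm that loses more people keeps proportionally more early, unimproved scores and looks worse even when dropout is random.

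**Working it through.** **Inputs from the protocol.** "A standardized mean difference of 0.44 was used"; "Using an α level of 0.05"; power 0.8; 44 evaluable, 52 enrolled; 1:1 allocation; clinically relevant difference 3 points.

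**Assumed, because not stated.** Two occasions and correlation ρ = 0.5 for the sizing (range 0.3 to 0.7 shown); f = 0.44/2 = 0.22.

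**1. Reproduce the planned size as an interaction test.** λ = f²·N·m/(1−ρ) = 0.0484 × 44 × 2/0.5 = 8.52, with 1 and 42 degrees of freedom. Power is 0.81 (N = 42 gives 0.795), so N = 44. Then 44/0.85 = 51.8, rounded up to 52. Both stated figures reproduce.

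With two arms and two occasions, f = 0.22 for the interaction means a difference in change of 4 × 0.22 = 0.88 SD. It is used here only because it reproduces the protocol's figure; whether it is a fair translation of 0.44 is a separate question.

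**2. Same inputs, arm term only, pre and post scores as rows.** The true arm difference is 0 at baseline and 0.88 SD afterwards, so the coefficient is (0 + 0.88)/2 = 0.44 SD. Its standard error is √((1+ρ)/2) × √(2/22) = 0.866 × 0.3015 = 0.261 SD. Noncentrality is 0.44/0.261 = 1.69 on 42 df, and power is 0.38. For the interaction it is 0.88/0.3015 = 2.92. About 124 evaluable participants would be needed for 80% power with the arm term.

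A simulation of 300 REML fits agrees: mean arm coefficient 0.42 with 37% rejections, against an interaction coefficient of 0.89 with 85% rejections (Wald tests).

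**3. More visits as rows.** Assume the effect builds linearly to Lab Visit #4 and then holds. Five rows (Lab Visit #2 to Lab Visit #4): mean (0 + 0.25 + 0.5 + 0.75 + 1)/5 = 0.50, so 0.44 SD. Seven rows (adding months 6 and 12): 4.5/7 = 0.643, so 0.57 SD. Power at N = 44:

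| ρ | Interaction, pre/post | Arm term, pre/post | Arm term, 5 rows | Arm term, 7 rows |
|---|---|---|---|---|
| 0.3 | 0.67 | 0.42 | 0.58 | 0.83 |
| 0.5 | 0.81 | 0.38 | 0.45 | 0.68 |
| 0.7 | 0.96 | 0.34 | 0.37 | 0.57 |

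**4. Lab Visit #2 not a row.** The arm term is then a baseline-unadjusted average over post-randomisation visits. With six such rows and the same profile, the mean is 4.5/6 = 0.75, so 0.66 SD. The standard error at ρ = 0.5 is √((1 + 5 × 0.5)/6) × 0.3015 = 0.230 SD; noncentrality is 2.87 and power is about 0.80. Power is not the problem in that case, but the test is still not the interaction.

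**5. Dropout with no true arm effect.** Assume Lab Visit #2 is a row, seven scheduled scores, a common improvement of D points that builds linearly to Lab Visit #4 and holds, and random loss after baseline or week 3. A participant with k scores has weight k/(1+(k−1)ρ). Example with D = 10, ρ = 0.5 and loss after baseline: completers have weight 7/4 = 1.75 and mean 6.43; dropouts have weight 1 and mean 0.
- 5% loss: 0.95 × 1.75 × 6.43/(0.95 × 1.75 + 0.05) = 6.24.
- 25% loss: 0.75 × 1.75 × 6.43/(0.75 × 1.75 + 0.25) = 5.40.
- Spurious arm difference: 0.84 points.

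Over D = 5 to 10 and ρ = 0.4 to 0.6, the shift is about 0.4 to 0.9 points for 25% against 5% loss, and about 0.2 to 0.5 points for 20% against 10%. Both splits average to the protocol's 15%.

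**The case against.** The strongest reply is that the sentence is an abbreviation. It does not say that arm is the only fixed effect and gives no model formula. The sentence before it speaks of scores between arms over time, and the trial was sized on an interaction. An arm-by-time model is a natural reading, and a journal article may leave the full formula to an analysis plan.

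Much of this stands. A reader might infer that the authors deliberately excluded time, or that the baseline score is certainly averaged into the treatment effect; the documents establish neither. That Lab Visit #2 is a response row is only implied, by the reference to time and the lack of a baseline covariate. A reader might also infer that dropout alone could produce a clinically relevant result. It could not in the scenarios examined: even a fivefold imbalance, which the protocol does not predict, stays under 1 point. Nor is power lost in every scenario. With seven rows, a persisting effect and ρ = 0.3, the arm term has power 0.83 against 0.67 for the pre/post interaction.

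The reply does not remove the discrepancy. The article chose to list the primary model's terms, and the list disagrees with its own sample size section. It also writes out the interaction for secondary outcomes a few sentences later.

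**Conclusion.** The point holds as an inconsistency in how the primary model is stated, and it should be fixed. Followed as listed, the model contains no coefficient for a difference in improvement and so does not test the hypothesis or the effect used for sizing. That conclusion does not depend on the correlation, the trajectory or the status of Lab Visit #2.

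The size of the harm does depend on them. If Lab Visit #2 is a row and only pre and post scores enter, power drops from 0.81 to 0.38 on the inputs that reproduce 44. With more visits and a lasting effect the loss is smaller, and if Lab Visit #2 is not a row it may be negligible. The dropout shift is real but modest. It matters mainly because the protocol says its analysis will account for differential loss, and a model without time does not do so even when the loss is random.

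**What to change.** In Intended statistical analysis, replace the sentence listing the terms with one that states fixed effects for arm, visit (categorical) and arm × visit, with participant as random effect. Keep REML and Kenward-Roger as they are. State that the Lab Visit #2 score is a response row, and name the arm × visit contrast from Lab Visit #2 to Lab Visit #4 as the primary test, consistent with the Sample size section.

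Optionally, constrain the arms to be equal at Lab Visit #2, or use that score as a covariate. This is a gain in precision rather than a correction: on the step 1 inputs, the baseline-adjusted comparison has power 0.91 against 0.81 for the interaction.

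The cost is a sentence or two of analysis wording, with no new data or participants. It should be settled before the data are analysed, so that the primary test is not chosen afterwards.
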